## Abstract

**Background:** The maturational period from age 10 to 14—often referred to as very young adolescents (VYAs)—represents a dynamic period of learning and neurobehavioral development as individuals transition from childhood to adolescence. This developmental period presents a window of opportunity for strategic investment to improve trajectories of health, education and well-being among young people. More specifically, neurodevelopmental changes during pubertal maturation influence neural circuitry involved in processing emotions, risks, rewards and social relationships. Technology can be leveraged to create social emotional learning experiences for VYAs and provide opportunities for flexible, distance learning in low-income countries. The aim of this study protocol is to detail how insights from developmental science can be used to inform the intervention design, implementation and evaluation of a distance learning, social emotional learning intervention for VYAs.

**Methods:** This study will be delivered to 500 VYAs in Temeke District, Dar es salaam. Study participants will watch culturally-relevant, animated videos on social emotional mindsets and skills and content will be paired with experiential learning activities over a period of 10 weeks. A nested smart-phone based study will practice learning social emotional skills and mindsets through engagement with multi-media material via the WhatsApp messenger application. Surveys and in-depth interviews will be administered to adolescents, their parents/caregivers and teachers before and after the intervention to evaluate the effect of the intervention on study outcomes.

**Discussion:** This study is among the first to provide results on how to effectively design a distance-learning intervention to promote social emotional learning and identity development within a low-resource context. The findings will provide substantial evidence to inform new intervention approaches that are effective in low-resource contexts and strategies to reach scale among similar programs invested in leveraging technology to support adolescent health and development.

**Clinical Trial registration:** Study registered with ClinicalTrials.gov. Identifier number NCT0445807.

## Introduction

The Lancet Youth Commission Report highlighted the need for investment in the largest generation of 10- to 24-year-olds in human history (1). By 2018, there were ~1.24 billion adolescents representing 16% of the global population (2). Research has often focused on older adolescents (15–19 years) and missed the opportunity to intervene earlier where targeted interventions may have a greater impact (3, 4). The rapid growth in social emotional learning and identity development during early adolescence begins during the onset of puberty. During this time, physical, cognitive and behavioral maturation presents unique opportunities for intervention. This rapid period of maturational changes is sensitive to social emotional learning and identity formation experiences (5). For example, early adolescence is a time when adolescents experience enhanced motivation to embrace novelty, master new learning, take risks, and seek social reward (6, 7). Plasticity of the adolescent brain allows for rapid and dynamic development that both shapes the ways that adolescents experience the world, and responds to these experiences through reorganization of neural circuitry involved in processing emotions, risks, rewards and social relationships (8, 9). These developmental changes can lead to lasting impacts over the lifespan.

In low-resource contexts, adolescents face additional stress and adverse life experiences. Findings from research suggest targeting very young adolescence rather than later adolescence, can better improve long-term health trajectories by attenuating risks for health that increase during later adolescence such as depression, anxiety, violence and forced sex (1, 10, 11). Further evidence suggests that interventions that target very young adolescents lower HIV/AIDS infection rates, decrease the number of unwanted pregnancies, and improve a variety of indicators of health and well-being (12–14). As a result, there has been an increasing focus in sub-Saharan Africa to target early adolescence to improve health trajectories and reduce gender-based health disparities (15). Tanzania is experiencing a surge in the youth population, with ~12.2 million children between the age of 7–17 years making up 20% of the total population. The total population in this age group is expected to double by 2055 (16).

Since the introduction of free primary education in 2001, Tanzania has made strides to improve access to education. Between 2004 and 2010, enrolment in secondary education tripled for girls and quadrupled for boys, and by 2012 over 8.7 million (71%) of children between 7 and 17 years were enrolled in school (17). While the introduction of free primary education has resulted in higher secondary education enrollment, it has also revealed important equity gaps. Only a third of children that start primary school complete the cycle in seven years. The transition rates largely favor boys, with ~21% of boys joining secondary schools compared to 16% of girls (17). The results of a child poverty study conducted in Tanzania found that 74% of children in Tanzania are affected by multidimensional poverty while 29% live in households below the monetary poverty line (18). These educational and economic challenges have important impacts on adolescent health and well-being in both the short and long-term.

In 2016, one in four adolescent girls aged 15–19 years had begun childbearing, reflecting a 4% increase in teenage pregnancy since 2010 (19). Unfavorable sexual and reproductive health outcomes for girls have been attributed to the fact that cultural norms in Tanzania often support inequitable gender norms, beliefs and behaviors, particularly around adolescent sexual and reproductive health and educational and employment expectations. Normative gender roles provide boys with more autonomy, freedom to engage in activities and employment outside of the home, whereas girls often have less autonomy and are encouraged to attend to home chores with limited encouragement to pursue career goals (20, 21). A cultural prototype of a chaste female student is highly valued. At the same time, female sexuality is perceived as a resource to meet financial needs which results in exploitation, and coerced, transactional sex. Disparities in educational enrollment patterns and outcomes have increased attention on addressing gender inequities during adolescent development to achieve positive health and well-being outcomes.

Delivering opportunities for social emotional learning experiences for very young adolescents using technology can enrich learning and be a flexible adaptation to complement learning in classrooms or to provide opportunities to continue learning when school-based learning is limited due to risks to health such as the COVID-19 pandemic. More recent research has focused on distance learning, as a modality to potentially replace in-person instruction (as has been required in many places due to COVID-19), and as a complement to traditional in-person education. Behavioral scientists underscore two mechanisms that motivate adolescents to use technology. First, rapid changes in adolescent's neurodevelopment motivate adolescents to seek autonomy, novel experiences, and exploration that can be scaffolded through use of digital technologies (22–24). Secondly, VYAs are increasingly invested in and learning about social relationships. Adolescents seek reward, respect and admiration from peers and are sensitive to feelings of rejection, disapproval and humiliation (25, 26). These experiences motivate adolescent social emotional learning and behavior. While peer relationships have greater importance along adolescent developmental trajectories, siblings, parents, extended family and the community also have the potential to enhance or diminish social emotional learning. An ecological model of adolescent learning is useful to consider opportunities for technology to leverage the sensitive window of early adolescent development across the individual, microsystem, mesosystem, exosystem and macrosystem (Figure 1). This research framework underscores opportunities to use technology to provide positive engagement with peers, family and the community in adolescent learning. Furthermore, use of technology within different contexts requires adaptation to ensure learning experiences are culturally resonant and tailored to very young adolescent in order to achieve effective intervention programming (22).

**Figure 1 F1:**
[figure not shown]
An ecological model of technology enabled learning opportunities for adolescents.

When the World Health Organization declared COVID-19 a global pandemic on 11th March 2020, many countries responded by enacting school-wide closures and/or distance learning alternatives that affected millions of children worldwide (27). How well schools and households are equipped to engage in remote learning differs greatly worldwide and within countries. In sub-Saharan Africa, penetration of mobile phone technology is high, with 80 subscriptions per 100 people, although only ~25% of these subscribers have access to internet services (28). In Tanzania, urban, younger, educated and English-speaking Tanzanians are most likely to use cell phones (29). While access to computers or tablets is limited, especially for young adolescents, the rapid uptake of technology provides new opportunities for learning (30). In 2016, the mobile operator Tigo Tanzania offered free WhatsApp access to its 10 million subscribers (31). Preliminary research with adolescents in Dar es Salaam and Mtwara indicates that adolescents ages 15–19 are increasingly using phones to access the internet (32). Adolescents are often among the earliest adopters of new technology and online learning platforms, however increased access to online information can accelerate both negative and positive developmental trajectories. Distance learning and technology can provide social emotional learning experiences that are designed to synergize with the rapid and dynamic changes in development that begin at the onset of puberty. These innovations include opportunities to enhance feelings of social reward and admiration, scaffolded learning that encourages risk taking, exploration and persistence, and, recognition of mastery of new skills.

Low-income countries face challenges to the effective utilization of technology including financial barriers to accessing technology, lack of regulation, long standing fear that technology will be used to access salacious content, and limited network connectivity. Amid these challenges, some promising remote learning programs are emerging. In Rwanda where radio reaches almost 99% of the population, lessons on primary-level literacy and numeracy are broadcasted daily for 20-min (33). Lessons are designed so that students can listen to content on their own, but parents and caregivers are encouraged to participate and support learning at home (34). One study in Turkey suggests that using WhatsApp Messenger application as a supplementary technology can increase the success of the students learning in the traditional classroom environment (35). Similarly, in Ghana, a program that uses WhatsApp Messenger to teach young learners found that a blended mobile learning structure that includes an intentional design and a step-by-step approach to teach both teachers and students can make communication easier and faster, including enhancing idea sharing among students (36).

WhatsApp is a free, internet-based messenger application that can be used to send multimedia messages like photos, videos, audio and simple text messages (37). Evidence shows that WhatsApp has the ability to increased student motivation and engagement around learning by using images to support information texts (35). In addition, this messaging service permits the unlimited and free sharing of multimedia. The WhatsApp platform is popular because it is highly interactive, allows timely feedback from instructors to the learner and permits attachments and sharing of classroom materials. Technology can also provide enhanced flexibility in instruction. For example, WhatsApp and SMS text-based systems can enhance or supplement learning access in more remote locations (38). These technology platforms appeal to adolescents because they provide both individual autonomy in learning and versatility in instructional content (39).

Unstructured Supplementary Services Data (USSD), is a session-based, real-time communication service that sends messages across a telecommunications network directly between a mobile client and an application server. USSD is similar to Short Message Service (SMS), however, USSD has a shorter turnaround response time, is cheaper and involves simple operations that can be assessed by older-model handset devices that are common in low-resource areas (40). Students interact with USSD by dialing a digit on the phone's keyboard in response to a question from the server. Messaging can be used between the mobile client and a pre-scripted program can to enhance interaction and support participatory learning. Other interventions have used different technologies such as tv and radio to reach students. In Sierra Leone an educational radio program (DevelopAfrica) was launched for students across the country, an initiative that was designed in response to the 2014 Ebola Outbreak (34).

Interactive technology can improve student engagement and has the potential to provide active, experiential learning that includes social interaction with peers. Platforms that facilitate social interaction are well-matched to the sensitive developmental window of early adolescence where adolescent neurodevelopment enhances motivation for social learning. Distance learning approaches offer opportunities to reach scale even in low-resource contexts. Investment in programs targeting early adolescence can leverage the sensitive window for learning that emerges with the onset of puberty through use of technology facilitated distance learning to improve adolescent health trajectories.

Our study follows the first intervention trial of the Discover Learning Intervention (*Discover Learning*), which aimed to support up to 500 very young adolescents and their families in Tanzania, with social emotional experiential learning content to support social emotional mindsets and skills that lead to healthy identity development. The intervention will be delivered over 10 weeks using a ten-module curriculum disseminated via distance learning and technology modalities. The specific target areas of adaptive social emotional mindsets and skills include: gender equity, teamwork, curiosity, growth mindset, persistence, purpose, utu, empathy and resilience, social responsibility and cooperation, and generosity. Learning materials are curated based on these ten social emotional mindsets and skills and will be translated into adolescent-friendly scripted videos aired to adolescents and their families via television and/or WhatsApp. Supplemental practice material includes a Parent/Caregiver-Youth workbook that will be disseminated to study participants and their families, with instructions to complete the activities individually or with near-peers, siblings, parents or extended family.

The first aim of *Discover Learning* is to provide a developmentally informed rationale for the design of the intervention and to detail the process related to the development, implementation and evaluation to enhance social emotional learning and identity development in very young adolescents. The primary research objective is to evaluate the extent to which a technology-based distance learning program can positively impact social emotional learning and identity development in very young adolescents. Our theory of change posits that if 10–14 year olds are exposed to information and material matched to the developmental window of very young adolescence, are engaged in activities that combine content and practice with their siblings/near peers, parents and community, there will be high impact improvements in outcomes for key social emotional skills and mindsets, enhanced equity in gender norms, beliefs and behaviors, and, health and well-being outcomes. These improved outcomes will help to set adolescents on early positive trajectories toward improved health, educational and economic outcomes. The results of this study will be used to: (1) determine the impact of *Discover Learning* on social emotional learning and identity development outcomes, (2) explore how technology can be used to amplify social emotional learning and identity development, and (3) examine how involvement of siblings/near peers, parents/caregivers and extended family can amplify study outcomes. *Discover Learning* is a strategic partnership between University of California Berkeley, Health for a Prosperous Nation (HPON), Camara Education and Ubongo Kids.

## Materials and Methods

### Study Setting

This study will be conducted in Dar es salaam, Tanzania. Tanzania currently has ~40.17 million sim card owners, representing 77% of the population (41). Dar es Salaam, which is the capital city of Tanzania, has five administrative districts. This research will be carried out in Temeke District, a peri-urban district. Study participants will be selected from four primary schools out of 114 schools within the district. The number of children enrolled in primary school in Temeke is 170,477; 49% are boys and 51% are girls. The average classroom size in Tanzania's primary schools is 80 students for each teacher (42). On 16 March 2020, the Ministry of Health of Tanzania announced the first case of COVID-19 (43). This announcement was rapidly followed by a directive to close schools indefinitely. In addition, measures such as prohibition of public gatherings and closure of recreational centers were established (44). Schools later reopened after 3 months of closure.

### Study Design

This protocol describes a study that will be conducted to test the impact of *Discover Learning*, a social emotional learning and identity development intervention for very young adolescents. The study employs an intervention design that leverages the principles of adolescent developmental science to improve early precursors of health inequities. A sample of 10–14 year old adolescents will be selected from four primary schools located in peri-urban areas of Temeke District in Dar es Salaam. Participants enrolled in *Discover Learning* will receive a distance learning intervention or will participate in a nested sub-group that includes additional smartphone-based content.

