### Sample

Based on the average population of each school, a cluster size of 100 will be required per school to detect a minimum detectable effect of 0.484 and a statistical power of 80% at a confidence level α = 0.05 for a two-tailed *t*-test (45). Assuming a participant dropout rate of 11.25% from the *Discover Learning* pilot study conducted in 2017 the final sample size will include 500 participants. The nested study will include all participants who have access to a smartphone with WhatsApp functionality. The study will be reported according to CONSORT guidelines.

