### Data Analysis

All quantitative data will be cleaned, coded and analyzed in Stata SE 16.0 (62). Statistical analysis will be conducted according to the Intention-To-Treat principle. Participants who do not complete all intervention modules due to attrition or who have missing data will be examined for inclusion in the final analysis. If <2% of the observations contain missing values on each variable and the pattern of missing values is random, then Listwise Deletion method will be used (63). If missing data is not determined to be missing at random, multiple imputation models will be used for analyzing adolescent data (64). All data will be examined for skewness or data non-normality. Multivariate regression models will be used to assess the effect of the intervention on study outcomes and will control for age, gender, socioeconomic status, school and household characteristics. Statistical significance for all analyses will be set at *p* < 0.05. Psychometric analysis of measures including exploratory and confirmatory factor analysis will be used to establish measure validity. Structural equation modeling (SEM) will be used to test structural paths between latent constructs. Potential mediating and modifying variables will be assessed. SEM models will be assessed for goodness of fit using indices including the root mean square error of approximation (RMSEA) (65), the comparative fit index (CFI) (66), the Tucker Lewis Index (TLI) (67) and the standardized root mean residual (SRMR). All qualitative data will be transcribed and translated verbatim from Swahili to English by trained translators. All participant identifiers will be removed from transcripts. All audio recordings of transcripts will be destroyed after transcription is completed and translation have been verified. Translations will be uploaded to Atlas.ti for analysis (68). A grounded theory approach will be used to identify emergent themes (69). The analytical steps will be conducted by two separate analysts. *Line-by-line coding of* each transcript will be used to identify initial codes that capture implicit meanings, and common relationships and significance between codes. Where appropriate codes will be left *in vivo* to preserve participant language and meaning. Next, *focused codes* will be developed from the most significant and/or frequent initial codes to make analytical sense of the data. *Axial coding* will be used to represent the content of focused codes and to connect relationships between codes, categories and concepts. During the application of focused and axial coding, analysts will meet to discuss and revise codes until consensus is reached. Researchers will write memos to capture connections and to construct analytic notes. Researchers will further hold discussions to help identify emergent themes and connections between themes through an iterative deductive process. Exemplar quotes will be selected to illustrate emergent themes. All transcripts will be stored in an access-controlled server that is located safely within the local implementation partner, HPON's Tanzania office and destroyed after 5 years.

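### As described, all 500 participants receive the programme and no comparator is stated, so the promised impact cannot be separated from background change

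*Protocol article*

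**What the plan says.** The objective is causal. The aims paragraph of the Introduction says: "The primary research objective is to evaluate the extent to which a technology-based distance learning program can positively impact social emotional learning". The first listed use of the results is to "determine the impact of *Discover Learning* on social emotional learning and identity development outcomes".

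The design described is a single treated population. The Abstract states: "This study will be delivered to 500 VYAs in Temeke District, Dar es salaam". The Sample section gives 500 as the final sample size. Under Study Design, participants "will receive a distance learning intervention or will participate in a nested sub-group that includes additional smartphone-based content". The Smartphone-Based Intervention Group section draws sixty children from inside the intervention group. They watch the same ten episodes and receive the activities by WhatsApp instead of on paper. The Abstract and the Baseline and Endline Survey section base the evaluation on measurements before and after the ten weeks.

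The analysis and reporting language is that of a comparative trial. Data Analysis says: "Statistical analysis will be conducted according to the Intention-To-Treat principle", and promises regression models for the intervention's effect. The Sample section says: "The study will be reported according to CONSORT guidelines". It also gives a minimum detectable effect of 0.484 for 100 children per school, with 80% power in a two-tailed t-test at 0.05.

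**The concern.** An impact is a difference between what happened and what would have happened without the programme. If every enrolled child receives it, the data hold nothing to stand for the second quantity. Several other causes act over the same weeks:

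- The Introduction itself describes this age as one of rapid maturation.
- The Study Setting section records a school closure after March 2020 and adds: "Schools later reopened after 3 months of closure". Baseline is in August and September 2020, so recovery from that closure may still be under way.
- The same children answer the same questionnaire twice.
- Answers go to researchers connected with the programme, so children may give the answers they think are wanted.

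If these shift the scores, the shift will be reported as impact. That affects the primary objective and every effect estimate.

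**Working it through.** **1. Is there any variation in exposure to the programme?**

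- Number treated (Abstract): 500. Total sample (Sample): 500. Untreated children: 500 − 500 = 0.
- The two groups in the text are episodes with paper worksheets, and the same episodes with WhatsApp activities. Both are the programme.
- Data Analysis adjusts for the child's age and gender, socioeconomic and household factors, and school. Adjustment can balance exposed against unexposed children. It cannot create the unexposed, so it does not help here.
- The sixty WhatsApp children against the rest is a contrast of delivery modes. It is selected on smartphone access and regular WhatsApp use, and it says nothing about programme against no programme.

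**2. Which design does the stated detectable effect fit?**

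Inputs from Sample: 4 schools × 100 = 400 children, 80% power, two-sided 0.05. The multiplier is 1.960 + 0.842 = 2.802. The text gives no ICC, so ICC values are assumptions. The design effect is 1 + 99 × ICC, which is 2.98 at an ICC of 0.02.

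| Design | Formula | Detectable effect (SD) |
|---|---|---|
| One group, before-after, no clustering | 2.802 × √(1/400) | 0.140 |
| One group, before-after, ICC 0.02 | 2.802 × √(2.98/400) | 0.242 |
| Two arms of 200, no clustering | 2.802 × √(2/200) | 0.280 |
| Two arms of 2 schools × 100, ICC 0.02 | 2.802 × √(2 × 2.98/200) | 0.4836 |

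The stated 0.484 matches the last row. The one-group design reaches 0.484 only at an ICC of about 0.11. The match depends on the assumed ICC: from 0.01 to 0.05 the two-arm figure runs from 0.395 to 0.683. It also depends on normal quantiles: with t on 2 degrees of freedom the figure at an ICC of 0.02 would be 0.926.

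(The total of 500 does not follow from 400 and 11.25% dropout, since 400/0.8875 = 451. That is a separate matter and does not affect this point.)

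**3. How easily does background change look like an effect?**

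Completers: 500 × (1 − 0.1125) = 443.75, taken as 444, or 111 per school. Suppose there is no programme effect and a background drift of d SDs of the change score. The drift sizes are assumptions; the protocol gives none. The probability of p < 0.05 for one outcome is P(|Z + d√n| > 1.96).

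- Children independent: n = 444 and √444 = 21.07.
- Assumed school ICC of 0.02: design effect 1 + 110 × 0.02 = 3.2, effective n = 444/3.2 = 138.75, square root 11.78.

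| Drift d | d√n, independent | P(significant) | d√n, ICC 0.02 | P(significant) |
|---|---|---|---|---|
| 0.10 | 2.107 | 56% | 1.178 | 22% |
| 0.20 | 4.214 | 99% | 2.356 | 65% |

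Adjusting for school may move the clustered figures back towards the independent ones.

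**The case against.** The strongest reply is that a comparator may exist outside the text available here. Figure 3, which is said to illustrate the study design, is not shown. RCT appears in the abbreviation list, the nested section refers to an intervention group, and the 0.484 fits two arms of two schools. This stands as a limit on certainty. A reader might infer that the trial definitely has no control arm, or that the detectable effect proves it once had one. The documents support neither, and the second inference rests on a chosen ICC. But a control arm in Figure 3 would contradict the Abstract, Study Design and Sample, so the text needs correcting either way. Whether a comparison group exists is also not a detail that an article leaves to a fuller document.

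A second reply is that intention-to-treat here means keeping every enrolled child. That is fair: the sentences that follow it concern unfinished modules and missing data. The term is loose rather than meaningless, and it does not supply a contrast.

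A third is that more than before-after change can be estimated. That is also true. Delivery mode, family involvement, and mediating or modifying variables can all be examined, so the second and third uses of the results are not all defeated. None of these identifies the programme against its absence.

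Finally, the drift probabilities are illustrations, not predicted error rates for this study.

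**Conclusion.** The point holds for the design as the text describes it. Mean change from baseline to endline can be estimated, but it cannot be attributed to the programme, so the primary objective and the first stated use of the results are not supported. This rests on the text alone, with Figure 3 unseen, and does not depend on any assumed number. The size is illustrative: with no true effect, drift of 0.10 to 0.20 SD of the change score produces a significant result 56% to 99% of the time with independent children, and 22% to 65% at an assumed ICC of 0.02. The intention-to-treat, CONSORT and sample-size statements read as if a comparison arm existed and are inconsistent with the rest of the text. The correction is needed because it changes what the trial may conclude.

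**What to change.** First, reconcile the Abstract, Study Design, Smartphone-Based Intervention Group, Sample, Data Analysis and Figure 3 on whether there is a comparator.

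If there is none:

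- Restate the primary estimand as mean within-child change from baseline to endline in an uncontrolled before-after study, and say that it will not be read as a causal effect. Change the aims to match.
- Replace the intention-to-treat statement with one that the analysis includes all enrolled children, whatever number of modules they completed.
- Replace CONSORT with a reporting guideline for non-randomised evaluations.
- Restate the detectable effect for a one-group before-after analysis, with its ICC.

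If there is a comparator:

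- Correct the Abstract, Study Design and Sample to describe it and how it was allocated.
- Define the effect as the between-group contrast.
- If allocation was by school, reconsider school as a fixed covariate in a model for endline or change, because it would be collinear with arm.

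The cost is wording and, in the first case, a less ambitious claim. Recruitment, delivery and data collection need not change.
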